### Inclusion and exclusion criteria (see Additional file 1: Appendices 1-4 for definitions/additional details)

Vietnamese MoH guidelines indicate that all suspected HFMD cases with Grade 2 or more severe disease should be admitted to a Pediatric Intensive Care Unit (PICU) or High Dependency Unit (HDU) facility for close observation. The guidelines also indicate that a peripheral arterial line should be inserted for invasive BP monitoring if there are any signs of ANS dysfunction. For patients with Grade 3 disease (that is, the group eligible for inclusion in this study), the pulse, BP, respiratory rate and pattern, oxygen saturation, and temperature must be monitored very closely, and the child should receive intravenous sedation with phenobarbitone, as well as a dose of 1 g/kg intravenous immunoglobulin (IVIG) as soon as possible, with a second dose of IVIG 24 h later.

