#### Laboratory assessments and diagnostic testing

The following laboratory tests (see Additional file 1: Appendix 9) are performed on site in the standard hospital laboratories or at the research laboratory of OUCRU in Ho Chi Minh City, except where specifically indicated below:Blood glucose and arterial blood gases are measured at least once daily or more frequently according to the clinical situation.Plasma magnesium and calcium concentrations are measured at baseline and 12 h after the start of the study infusion, then once daily for the remaining 72 h.Plasma electrolytes, creatinine, CKMB and Troponin I are measured at baseline and once daily thereafter.Samples for plasma catecholamine (epinephrine and norepinephrine) concentrations are collected at baseline and then once daily for 72 h, and stored frozen for subsequent analysis in batches. Similarly, a 5-ml aliquot of urine is collected each morning for measurement of urine catecholamines. All urine is collected in appropriate collecting bottles (containing 10 to 15 ml 6 M HCl as preservative) by the bedside and the total volume is recorded at the end of the 24-h period, before the 5-ml aliquot is taken for storage at −20 °C.Samples for plasma cytokine measurements (including IL1, IL6, IL13, and TNF alpha) are collected and stored at −20 °C at baseline and at 12 h and 24 h after starting the MgSO_4_/placebo, with a final sample obtained on discharge from hospital.A nasal/throat swab and a rectal swab are obtained at enrollment, for enterovirus PCR.Serological testing for EV71 and related serotypes within the *Human enterovirus A* species will be done on plasma samples collected at enrolment and discharge. This work will be done in collaboration with laboratories at Duke-NUS in Singapore.With separate consent, cells from participant plasma samples are separated and stored for assessment of host genetic factors associated with disease severity using exome sequencing at The Wellcome Trust Sanger Institute, UK.

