### Statistical considerations

#### Sample size

During 2011, approximately one-third of patients with Grade 3 HFMD managed at HTD (48/140, 34 %) and CH1 (48/148, 32 %) required milrinone for ANS dysregulation with hypertension, and in 9/48 (19 %) of the HTD cases and 10/48 (21 %) of the CH1 cases, milrinone, when used alone, failed to control the hypertension (personal communication, [name] [name]). Following introduction of new Vietnamese MoH management guidelines to commence intra-arterial BP monitoring early (at the first sign of autonomic disturbance), among 16 children managed in this way at HTD over a 2-month period, 12/16 patients developed Stage 1 hypertension, and seven of these 12 cases developed Stage 2 hypertension and were treated with milrinone. Based on this observation (that is, that 7/12 children with Stage 1 hypertension progressed), for the sample size calculation for this study, we estimated a progression rate of 50 % in the control arm.

With respect to the hypothesized treatment effect, little direct information exists for the actual scenario we plan to investigate, that is, the influence of MgSO_4_ commenced at Stage 1 hypertension on subsequent control of SBP and progression to severe disease. In the case series described earlier, when MgSO_4_ was added to the treatment regimen of patients with poorly controlled hypertension, despite high-dose milrinone, in all cases, the SBP reduced within 30 to 60 min and thereafter remained stable on a continuous MgSO_4_ infusion. In the tetanus study mentioned above (in which the study drug was given to patients with severe tetanus requiring a tracheostomy), the requirement for additional therapy to treat ANS dysfunction was reduced from 14/97 (14 %) in the placebo group to 3/97 (3 %) in the MgSO_4_ group, although the need for assisted ventilation was similar in the two groups. Thus, indirect evidence suggests that the effect size of the proposed intervention may be large; we therefore estimate that use of MgSO_4_ could reduce the risk of progression by > 50 %.

Based on 1:1 randomization, an anticipated relative reduction in the risk of progression of 50 % (from 50 % in the control arm to 25 % in MgSO_4_ recipients), 90 % power, and a two-sided 5 % significance level, 85 patients per treatment group are required. To allow for some violations of our assumptions and losses to follow-up, we plan to recruit 190 patients (95 patients per treatment arm) into the study.

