#### Statistical analysis

All planned statistical analyses will be pre-defined in a detailed statistical analysis plan, which will be finalized prior to unblinding the trial. The primary analysis population will include all randomized patients who commenced the loading dose infusion of the study drug, and analysis will be according to the randomized treatment arm (intention-to-treat). A per protocol analysis will also be performed, including all subjects who complete the full treatment schedule for 72 h or if death or one of the pre-specified criteria for stopping the study drug occurs within 72 h. An additional analysis will also be performed in the subgroup of patients with confirmed EV71 infection. The primary endpoint of disease progression will be compared between the two treatment arms based on logistic regression with the treatment assignment as the only covariate. As disease progression is evaluated in a short time frame, that is, within 72 h of study drug initiation, we expect to lose only a minimal number of patients to follow-up before that time point and will analyze these patients according to their last recorded disease status. We will also perform regression analysis, including a number of baseline covariates – age, sex, BMI, day of illness at study entry, study site, and baseline severity assessed in terms of an internationally recognized score (PRISM III).

Predefined secondary endpoints and exploratory investigations will be compared between the two treatment arms based on linear regression for continuous endpoints, logistic regression for binary endpoints, and Cox regression for time-to-event endpoints. For laboratory markers, analyses will be adjusted for the pre-dose value of the respective marker. For host genetics analyses in this sample, putative severity alleles will be detected by filtering and comparison with reference data from control groups including the 1000 Genomes Project. For alleles with significant enrichment among severe cases, validation will be attempted using samples from other cohorts with severe HFMD.

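### The host-genetics contrast cannot separate alleles for HFMD severity from alleles for HFMD susceptibility, yet its hits are labelled putative severity alleles

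*Protocol article*

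**What the plan says.** Under Laboratory assessments and diagnostic testing, the protocol article gives the purpose of the stored cells as "assessment of host genetic factors associated with disease severity using exome sequencing". This needs its own consent: "With separate consent, cells from participant plasma samples are separated and stored".

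Under Statistical analysis, detection is described thus: "putative severity alleles will be detected by filtering and comparison with reference data from control groups including the 1000 Genomes Project". Follow-up is described thus: "For alleles with significant enrichment among severe cases, validation will be attempted using samples from other cohorts with severe HFMD".

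The severity range of the sequenced children follows from Inclusion and exclusion criteria, which speaks of management "For patients with Grade 3 disease (that is, the group eligible for inclusion in this study". Their number is capped by Sample size: "we plan to recruit 190 patients (95 patients per treatment arm) into the study".

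The 1000 Genomes Project is the only control group named. No HFMD patients of lower grade are mentioned as a comparator, either for detection or for validation.

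**The concern.** The aim is to find alleles associated with severity. The matching null hypothesis is that, among children who have HFMD, allele frequency does not differ by severity. A comparison of Grade 3 children with population controls tests something else: whether Grade 3 children have the allele frequencies of the reference population.

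That second null is false for a true severity allele. It is also false for an allele that raises the chance of infection, or of clinical HFMD of any grade, and then has no influence on how severe the illness becomes. Rejection therefore does not say which kind of allele has been found.

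The validation step has the same gap. A pure susceptibility allele is as enriched in other severe cohorts as in this one, so it would replicate. At stake is the label on the hits, and whether later work treats susceptibility alleles as determinants of severity.

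**Working it through.** **The plan's own figure.** The genetic analysis has no stated sample size, threshold, power or panel size. The only figure to reproduce is the trial size, which caps the number of cases. From Sample size: "90 % power, and a two-sided 5 % significance level, 85 patients per treatment group are required", with progression of 50 % against 25 %.

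- Uncorrected: n = [1.960·√(2·0.375·0.625) + 1.282·√(0.25 + 0.1875)]² / 0.25² = 76.7.
- With continuity correction: (76.7/4)·[1 + √(1 + 4/(76.7·0.25))]² = 84.5, rounded up to 85 per arm. This matches.
- Recruitment is 190 in total, so there are at most 2 × 190 = 380 case alleles per autosomal site. Separate consent can only lower this.

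**What each stated contrast can show**

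| Step | Group 1 | Group 2 | Does severity vary among HFMD patients? |
|---|---|---|---|
| Detection | Grade 3 participants | population reference data; other control groups unnamed | No, for the control named |
| Validation | other severe HFMD cohorts | not stated | No, as stated |

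**Size for an allele with no effect on severity.** Assumed, because the article gives none of them: population frequency f = 0.10; odds ratio (OR) for HFMD of any grade 1.5 or 2; panel of 100, 500 or 2,500 people; two-sided test on allele counts.

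Case frequency: p₁ = OR·f / (1 − f + OR·f).
- OR 1.5: 0.15/1.05 = 0.143.
- OR 2: 0.20/1.10 = 0.182.

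Rejection probability: Φ[(d − c·SE₀)/SE₁] + Φ[(−d − c·SE₀)/SE₁]. Here d = p₁ − f, c is the two-sided critical value, SE₀ is the pooled standard error and SE₁ the unpooled one.

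Worked case, OR 2 and a panel of 500 (1,000 alleles):
- d = 0.0818; pooled frequency (380·0.1818 + 1000·0.10)/1380 = 0.1225; SE₀ = 0.01976; SE₁ = 0.02194.
- Alpha 0.05: (0.0818 − 1.960·0.01976)/0.02194 = 1.96, so rejection is 97.5 %.
- Alpha 5e-7: (0.0818 − 5.026·0.01976)/0.02194 = −0.80, so rejection is 21 %.

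Rejection for panels of 100 / 500 / 2,500:

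| Odds ratio | alpha 0.05 | alpha 0.0001 | alpha 5e-7 |
|---|---|---|---|
| 1.5 | 30 / 61 / 73 % | 0.5 / 6 / 14 % | 0.01 / 0.5 / 1.9 % |
| 2 | 76 / 98 / 99 % | 8 / 59 / 82 % | 0.4 / 21 / 49 % |

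Every entry exceeds its nominal level (5 %, 0.01 % and 0.00005 %), but the absolute rate falls steeply as the threshold tightens.

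**With a milder-HFMD comparator.** If the controls are HFMD patients of lower grade from the same population, a susceptibility-only allele has the same frequency in both groups. Then d = 0 and rejection returns to alpha.

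**A contrast within the trial.** At the planned rates, 190 × (0.50 + 0.25)/2 = 71.25 children progress and 118.75 do not. For an allele with odds ratio 2 for progression and frequency 0.10 in non-progressors, d = 0.0818, SE₀ = 0.0357 and SE₁ = 0.0377. Power is Φ[(0.0818 − 1.960·0.0357)/0.0377] = 62 % at alpha 0.05, and 6 % at alpha 0.0001 (c = 3.891).

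**The case against.** The strongest reply is that the text claims less than the concern needs. It speaks of control groups in the plural, introduced by the word *including*, so local, infected or mild-disease controls are not ruled out. It calls the alleles putative, applies filtering, and only attempts validation. This describes candidate screening. The article is also a condensed text that defers detailed analyses to a statistical analysis plan that is not shown.

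Much of this stands, and it rules out four stronger readings that a reader might infer:

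- *Susceptibility alleles will be declared severity alleles.* The documents support only that they can be carried forward under that label.
- *Ancestry differences will produce false severity alleles.* This depends on which panel samples are used and on any adjustment for population structure. Both are ordinary analysis-plan content, and nothing says the panel will be unmatched.
- *The error rate is 30 to 99 %.* Those figures hold at a single-variant 5 % threshold, which the article does not state and which would be lax for an exome. At 5e-7 the range is 0.01 to 49 %.
- *Comparing progressors with non-progressors in the trial would test the stated question.* It tests 72-hour progression among treated children who are already Grade 3. An allele that acts on the step from Grade 1 or 2 to Grade 3 is a severity allele and could show nothing there. Power is also low.

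What the reply does not remove is the mismatch between the named contrast and its label. Adjustment for population structure cannot turn a population panel into a non-severe HFMD comparator. Nothing stated about filtering separates susceptibility from severity, and the validation cohorts are specified as severe.

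**Conclusion.** The concern holds in a limited form. Unless a milder-HFMD group is among the unnamed controls, the stated detection and validation steps cannot tell susceptibility alleles from severity alleles, and the label claims more than the contrast supports. The problem lies in a contrast that the article itself sets out, so it is not a matter of detail left to another document.

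The direction is certain. The size is not, because panel size, effect size and threshold are all assumed, and 190 cases is an upper limit. The calculated rates exceed nominal at every threshold tried, but at a strict threshold with a modest effect they are small in absolute terms.

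The consequence is confined to an ancillary, separately consented analysis that appears in neither the objectives nor the named endpoints. The primary endpoint, the sample size, the treatment comparison and the safety conclusions are untouched.

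**What to change.** Amend the host-genetics sentences under Statistical analysis as follows.

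1. Describe alleles that differ from population controls as *enriched in severe HFMD relative to the population*.
2. Reserve *severity allele* for those supported by a contrast with milder HFMD from the same population, in detection or in validation, where such samples exist. If the unnamed control groups already include milder HFMD, say so.
3. Add a regression of 72-hour progression on allele count in the sequenced participants, adjusted for treatment arm and genetic principal components. Present it as supportive evidence and not as a condition of the label. State that it addresses progression among Grade 3 cases only and has low power.

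The cost is wording plus one regression on data already planned for collection; no extra patients are needed. The downside is that fewer alleles will earn the severity label, and possibly none if no milder-HFMD samples can be found.

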### Ethical considerations

#### Ethical review

The study is being conducted in compliance with the current revision of the Declaration of Helsinki (Seoul 2008) and the terms of approval of all supervising Ethical Committees. The study protocol and its associated documents have been reviewed and approved by the following committees: The Vietnam Ministry of Health’s Evaluation Committee on Ethics in Biomedical Research, The Ethics Committee of the Hospital for Tropical Diseases, The Science and Ethics Committee in Biomedical Research of Childrens Hospital 1, and the Oxford Tropical Research Ethics Committee (OxTREC, University of Oxford). The study is managed by the OUCRU Clinical Trials Unit in compliance with the ICH Guidelines of Good Clinical Practice, the Vietnamese Ministry of Health Guidelines of Good Clinical Practice and the relevant institutional and regulatory requirements. The study is sponsored by the University of Oxford and appropriate insurance backed indemnity is in place with respect to the University’s role as research sponsor.

#### Informed consent (Additional file 1: Appendix 7)

The study staff members discuss the study with the accompanying parent/guardian, describing the purpose, procedures, possible risks/benefits, the rights and responsibilities of participants, and alternatives to enrollment, and the family are invited to ask questions. Those who agree to participate are asked to sign/date an Informed Consent Form, with a second copy to keep.

As indicated above, because HFMD may progress rapidly, the parents/guardians of potentially eligible patients are given study information shortly after admission, so later if the child fulfils the necessary enrolment criteria, the staff can discuss the study again, allowing the family at least 1 to 2 h to decide. Families of children presenting with Stage 2 hypertension are given up to 30 min to decide, but since insertion of the access lines necessary for standard care takes at least 30 min, this process does not result in delay. All families are given the opportunity to review the study information on the PIS with a study doctor at least once more 12 to 36 h after enrollment.

#### Confidentiality / participant protection

Personal information is recorded for the purpose of consent and to enable follow up of treatment outcomes. Access to identifying information is restricted to site-specific study staff and the clinical care team, and only anonymized data are entered into the study database. All other study documents are identified by the subject number and patient initials only. All documents are stored safely in secure, confidential locations. Data recorded on paper are entered on site into the database in accordance with standard operating procedures and are monitored for accuracy.

#### Patient benefits & compensation

For all trial participants, the medical costs associated with diagnosis and treatment of HFMD are covered from the time that the parent/guardian agrees to allow their child to enroll in the study until discharge but do not include the medical costs related to previous treatment decisions made before enrollment. All trial-related procedures are covered by the study, and patients are reimbursed the cost of local transport to attend for the follow-up visit according to OUCRU compensation policy. This policy reflects the actual cost of transportation plus modest compensation for time lost from work.

#### Withdrawal of participants from the study

Dedicated study staff members are employed to support parents/guardians to meet study visits and ensure that all trial outcome data are collected. Parents/guardians of the study participants may voluntarily withdraw from the study for any reason. If this occurs, the child will be managed in accordance with standard clinical care guidelines. With the agreement of the parent/guardian, a clinical assessment will be performed and recorded at the time of withdrawal, and the reason for withdrawal will also be recorded in the CRF.

#### Communication/dissemination policies

The study protocol and materials will be made available via publication. The results of the study will be reported in international medical journals with authorship determined according to the guidelines of the International Committee of Medical Journal Editors. Participants will not be individually informed of the results. The overall study findings will be published in both English and Vietnamese and reported to the Department of Health of Ho Chi Minh City. The researchers will also convey the research results to the community in Vietnamese through the OUCRU website and through talks and articles written and published in the mainstream media.

#### Safety reviews

An independent Data and Safety Monitoring Board (DSMB) has been established, consisting of qualified individuals with the necessary knowledge of local treatment guidelines, clinical trials, and statistics, and operates in accordance with a written DSMB charter. The DSMB reviewed and approved the conduct of the study after enrollment of the first five, and subsequently, the first 20 patients. In due course the DSMB will perform a formal safety review after 30 patients have been enrolled (phase 1), including unblinded summary tables of SAEs, AEs, or event reports submitted to the DSMB, plus an analysis of overall clinical outcome based on the interim analysis plan. If no safety concerns are identified, recruitment will expand to include CH1 (phase 2). A further DSMB review will take place after 100 patients have enrolled in the study, with additional safety reviews performed annually or at the discretion of the DSMB based on available data and ongoing reporting. Unless the benefit of MgSO_4_ is shown “beyond reasonable doubt,” no formal stopping rule for efficacy is foreseen; the Haybittle-Peto boundary, requiring *P* < 0.001 at interim analysis to consider stopping for efficacy, will be used as a guide.

## Discussion

Although HFMD has become a major contributor to childhood morbidity and mortality in Vietnam, current management strategies rely on guidelines that are based primarily on expert opinion plus two small clinical intervention studies, one of which used retrospective controls. The efficacy of milrinone, an expensive drug with a significant toxicity profile, for management of ANS dysregulation in children with HFMD and brainstem involvement is unclear, and MgSO_4_, an alternative therapeutic agent that is cheap, safe, and easily available may be more effective.

The current Vietnamese MoH guidelines specify that milrinone should be given to children with HFMD and Stage 2 hypertension due to ANS dysregulation. Although a direct comparison of MgSO_4_ with milrinone might have been illuminating, we were constrained to ensure that none of these very sick children be denied the possible benefit of milrinone. Thus, enrollment to this study was designed to be early, when hypertension is first identified (at Stage 1), so that in the event of treatment failure, the MoH treatment guidelines can still be applied. If MgSO_4_ is shown to be effective in controlling ANS dysregulation at this early stage, and in preventing deterioration/development of severe complications, this would be important to pediatric care throughout the Asian region. Additionally, it might be possible later to consider a direct comparison between milrinone and MgSO_4_ in HFMD cases with established severe hypertension (Stage 2).

Sample size estimates for a study of this nature, where reliable baseline outcome data are lacking, are always difficult to calculate. We used indirect evidence from use of MgSO_4_ in other conditions, together with the data from the small, unblinded pilot study in severe HFMD cases that failed to respond to maximum dose milrinone, to estimate the effect size of the proposed intervention. We acknowledge that the proposed effect size is large, but it does appear reasonable based on this evidence. Moreover, given the epidemic situation in Asia, we chose not to delay starting the study further by doing a formal pilot study.

Vietnamese guidelines for the management of HFMD are regularly reviewed, and the MoH Guidelines Committee strongly supports the idea for this study. If the results are positive, it is likely that use of MgSO_4_ would be incorporated promptly into the local guidelines, with the potential for rapid adoption by neighboring countries experiencing similar severe HFMD outbreaks.

